#### *The secondary outcomes* include

(1) *Depressive symptom score at 3 and 12 months*, measured by the PHQ-9 [31]. The PHQ-9 scores each of the 9 depressive symptoms in the past two weeks as “0” (not at all) to “3” (nearly every day) with total scores ranging from 0 to 27. The PHQ-9 has excellent internal reliability (Cronbach’s α = 0.89) [31]. (2) C*hange in self-help score* measured by the Self-management Strategy Use Scale (SSUS). The SSUS assesses the frequency of using each of the 14 evidence-based self-help strategies. Frequency of use is rated on a 5-category scale. The SSUS has good internal consistency (Cronbach’s α = 0.80). (3) *Mental health services use* over the study period. Standard questions used by Statistics Canada about in-patients and out-patient psychiatric care, ED mental health services use, and contacting physician and other health professionals for mental health and emotional problems. (4) *Sick leave and productivity* measured by the WHO’s Health and Work Performance Questionnaire (HPQ) which collects information about number of sick leave days and presenteeism in the past 30 days [39]. The HPQ had good concordance with the corporate archival productivity measures [39].

*Other measures* include age, biological sex at birth (male, female, intersex, other), gender [man, woman, Indigenous or other cultural identities (e.g., two spirit), others (e.g., gender fluid, non-binary)] [37] race/ethnicity, marital status, employment status, and levels of education and income, number of hours for caring family members each week, history of MDE, symptoms of anxiety, comorbid physical health conditions and self-efficacy. *Anxiety symptoms* will be measured by GAD-7 [38]. *The GAD-7* is a valid and efficient tool for screening for generalized anxiety disorder and assessing its severity in clinical practice and research. A higher score indicates more severe anxiety symptoms. The internal consistency of the GAD-7 was excellent (Cronbach α = 0.92). Test-retest reliability was also good (intraclass correlation = 0.83) [38]. *Self-efficacy* will be measured using the General Self-Efficacy scale [40, 41]. The lifetime version of the CIDI will be administered at baseline to ascertain *history of MDE.*

The collected data will be stored at the secured cloud drive of Dalhousie University. Only the interviewers and coaches will have access to individual data. Only de-identified data will be used for data analysis and only aggregated data will be published and presented.

### Statistical analysis

As the intervention is conducted in males and females separately, data will be initially analyzed in males and females separately. We will first compare the groups in baseline demographics, socioeconomic and clinical characteristics, and missing values. To follow the CONSORT guidelines for reporting RCTs [42] we will perform both complete case and intent-to-treat (ITT) analyses to allow readers to interpret the effect of the intervention. In ITT analysis, we will include all participants with the group status they are originally assigned. Following the recommendations published in the N Engl J Med [43], and BMJ [44], missing values will be imputed using multiple imputation with 20 imputed datasets.

The proportions of MDE at 12 months (primary objective) and at 3 months will be estimated and compared between the intervention and control groups. For the primary objective, mixed-effects logistic regression modeling will be performed using combined imputed datasets based on Rubin’s rules, adjusting for the effects of demographic and socioeconomic characteristics, baseline PHQ-9 score, predicted risk of MDE, caregiving burden, and comorbid physical conditions [45]. Additionally, it will account for within-participant correlation over time through the incorporation of random effects. Within-and between‐group effect sizes will be estimated by computing Cohen’s h [46]. The analyses will be repeated among complete cases. Sensitivity analyses (best-worst and worst-best) will be conducted under the assumption of missing not at random [43, 44]. The PHQ-9 mean scores at 3- and 12-months, the changes in SSSU scores and the proportions of mental health service use in the past year between the groups will be compared using t test and Chi square test, respectively (secondary objective #1 & #2). We will investigate if self-efficacy is a moderator in the relationships between the intervention and outcomes by including a two-way interaction term between self-efficacy and intervention status in the models (secondary objective #3). If no evidence supports moderation by self-efficacy, we will examine if self-efficacy plays a role of mediator using structural equation modeling.

As part of sex-/gender-based analysis, when analyzing the data by biological sex, we will first describe gender identity and the gender role related variables (employment status, education, income levels, and caregiving burden) to identify any gender differences and intersectionality (overlapping and interdependence among the gender role related factors) within and between the groups. In sex specific analysis, we will control the effects of gender and gender role related variables in the models. Additionally, we will evaluate the impact of the intervention on the risk of MDE by gender through stratified analysis and logistic regression modeling. As exploratory analyses, we will compare the outcomes between groups in completers, by history of MDE, and by gender identity.

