### Inclusion criteria

(1) no MDE at baseline, or full remission for 2 months for those who had a past MDE (see below the question). (2) Aged 18 and 65 years. (3) At high risk of MDE based on the depression risk calculators (predicted risk of 6.5%+ for males and 11.2%+ for females) [29], which represent the top two deciles of male and female populations in Canada [29] (4) Agreement to be contacted for follow-up assessments, and (5) no language barriers to English or French. The status of remission will be assessed by the question: “In the past 2 months or longer, has your mood been much improved or back to normal AND you DIDN’T have the symptoms?” This question was adopted from the US NESARC study [30]. Although the risk calculators are sex-specific, our recruitment will be sex and gender inclusive; the recruitment is open to all sexes and genders.

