### Follow-up assessments

Participants will be followed and assessed at 3- and 12-month so we can assess the short- and mid-term effects of the intervention. The follow-up assessments will be conducted via telephone. After each assessment, the following materials will be mailed to all participants of the two groups: (1) a thank-you letter, including the date of the next interview, and (2) $20 incentive as appreciation for their participation. Participants in the control group will receive the same package as those in the intervention group.

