### Primary and secondary outcome measures

*The primary outcome* is the *proportion of MDE at 12-months*, measured by the 12-month version of CIDI-MD [36]. This version of CIDI is a fully structured diagnostic interview for mental disorders in the past 12 months based on the DSM-IV criteria, and has been widely used in population mental health surveys conducted by Statistics Canada and by others [36].

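### The primary model has random effects over time, but the primary outcome is one 12-month MDE status per participant, so its odds ratio is either not identified or not the 12-month contrast the trial was sized on

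*Protocol article*

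**What the plan says.** All places are in the protocol article.

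- **Outcome.** Under Primary and secondary outcome measures, the primary outcome is the proportion with MDE at 12 months, "measured by the 12-month version of CIDI-MD". The instrument is described as a "fully structured diagnostic interview for mental disorders in the past 12 months". Given at month 12, it yields one yes/no value per person covering the whole follow-up.
- **Assessments.** Follow-up assessments: "Participants will be followed and assessed at 3- and 12-month". Month 3 is therefore the only other post-baseline occasion. The recall window of the 3-month MDE is not given.
- **Entry.** Inclusion criteria require "no MDE at baseline, or full remission for 2 months for those who had a past MDE", so nobody enters in a current episode.
- **Analysis.** Statistical analysis opens with: "The proportions of MDE at 12 months (primary objective) and at 3 months will be estimated and compared". It continues: "For the primary objective, mixed-effects logistic regression modeling will be performed using combined imputed datasets", lists the adjustment covariates, and adds: "Additionally, it will account for within-participant correlation over time through the incorporation of random effects". It also says that "effect sizes will be estimated by computing Cohen’s h", which is a contrast of two proportions.
- **Sample size.** Sample size calculation assumes 12-month female incidence of 1.7% v 9.7% and derives 131 per group, 262 in total.

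**The concern.** A random effect for correlation over time needs at least two outcome records per person. The primary outcome supplies one. A current-MDE record at baseline would add no outcome information, because eligibility excludes current episodes. The only remaining candidate is the 3-month MDE, but months 0 to 3 lie inside the 12-month recall window. With consistent reporting, everyone who has an episode by month 3 is also a 12-month case. A random-intercept logistic model is poorly suited to such nested outcomes: it can explain the missing pattern (yes at 3 months, no at 12) only by enlarging the random-effect variance.

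At stake is the headline effect estimate. The odds ratio from this model could depend on where the software stops, or could describe something other than the 12-month difference in MDE risk that defines the outcome and underlies the sample size.

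**Working it through.** **1. The plan's own figure.** Two independent proportions, two-sided α = 0.05, power 0.80 (the printed β = 0.80 read as power), pooled variance under the null, mean proportion (0.017 + 0.097)/2 = 0.057:

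n per arm = [1.960·√(2 × 0.057 × 0.943) + 0.842·√(0.017 × 0.983 + 0.097 × 0.903)]² / 0.08² = 130.7, rounded up to 131, or 262 in total. This matches. The calculation uses one 12-month outcome per person and no repeated measures.

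**2. Target on the odds-ratio scale.** log OR = logit(0.017) − logit(0.097) = −1.83, so OR = 0.161. At 200 per arm (250 per arm per sex × 80% response), SE = √[1/(200 × 0.017) + 1/(200 × 0.983) + 1/(200 × 0.097) + 1/(200 × 0.903)] = 0.597. The expected 95% CI is exp(−1.83 ± 1.96 × 0.597) = 0.050 to 0.519. A single-level logistic model on the 12-month record estimates this, before covariates.

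**3. Mixed model, one record per person.** There is no within-person replication, so the data do not identify the random-intercept variance.

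**4. Mixed model, 3- and 12-month records, fully nested.** Model: logit P(MDE) = b0 + b1·time + b2·arm + u, with u ~ N(0, SD²). It was fitted by numerical integration to expected counts at 200 per arm. Twelve-month risks are the protocol's 9.7% v 1.7%. *Assumption:* 25% of MDEs occur by month 3 (2.425% v 0.425%) and all are re-reported at month 12.

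| SD held at | −2 log-likelihood | arm log OR | arm likelihood-ratio χ² | implied 12-month risks |
|---|---|---|---|---|
| 2 | 198.1 | −2.28 | 14.3 | 9.4% v 1.7% |
| 4 | 190.0 | −3.58 | 13.3 | 9.6% v 1.7% |
| 8 | 187.8 | −6.64 | 13.0 | 9.6% v 1.7% |
| 16 | 187.6 | −13.02 | 12.9 | 9.6% v 1.7% |
| 32 | 187.6 | −25.91 | 12.9 | 9.6% v 1.7% |

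The likelihood improves and then flattens, with no finite maximum in practice. The log OR grows roughly in proportion to the SD (ratio about −0.81 at SD 16 and 32). The single-record logistic model gives a χ² of 13.1. Adding an arm-by-time term does not help: the 12-month log OR is −6.76 at SD 8 and −26.3 at SD 32.

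**5. Not fully nested.** *Assumption:* 20% or 40% of 3-month cases are not re-reported at month 12. The fit is then finite. Without an arm-by-time term the OR is 0.031 or 0.068; with one, the 12-month OR is 0.028 or 0.063. The marginal value is 0.161.

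**6. Early effect only.** *Assumption:* 5% v 1% at month 3, 9.7% in both arms at month 12, same 20% or 40% discordance. Without an arm-by-time term the arm OR is 0.62 or 0.64, although the 12-month risks are equal. With the term, the 12-month OR is 1.02 or 1.01.

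**The case against.** **The records and terms are not stated.** The article does not say that the 3-month record is stacked or that an arm-by-time term is absent, and such detail is commonly left to an analysis plan. This stands for the mixing of time points, which is conditional on that term being left out. It does not remove the mismatch: the article itself prescribes random effects over time for the primary objective, and with only one record they cannot be estimated.

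**A yes at 3 months and a no at 12 is possible.** A reader might infer that this pattern is ruled out. The documents do not support that. The 3-month recall window is unstated. If the 12-month instrument is also used at month 3, it reaches about nine months before randomisation and could pick up past episodes in people who entered in remission. Early episodes may also go unreported at 12 months. The runaway variance therefore depends on consistent re-reporting.

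**The inference survives the runaway.** A reader might also infer that the whole primary result would be an artefact. Step 4 shows otherwise: with a similar effect at both times, the arm χ² and the implied 12-month risks stay close to the single-record analysis and the true risks. What fails is the odds ratio.

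**The 12-month proportions are compared anyway.** This is true, and Cohen's h is a marginal contrast. But the model named for the primary objective is the mixed one, so the adjusted primary estimate would not match that comparison. A participant-specific odds ratio is not wrong in itself, and a covariate-adjusted logistic odds ratio is conditional too. The objection here is that the random effect has no role with a single outcome, and that a second record brings the problems above.

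**Conclusion.** The point holds as a mismatch within the protocol. The primary outcome and the sample size concern one 12-month status per person, while the primary model is built for repeated measures.

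- **One record per person:** the random-effect variance is not identified.
- **Two records, consistently nested:** the reported odds ratio is arbitrary, with a log OR from −2.28 (SD 2) to −13.02 (SD 16) against −1.83, while the arm test and 12-month risks change little.
- **Two records, imperfectly nested:** the odds ratio can be finite but is participant-specific (0.03 to 0.07 against 0.161 in the cases tried). Without an arm-by-time term, an early-only effect appears as a non-null arm effect.

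The 12-month risks are the protocol's own. The 25% share by month 3, the 20–40% discordance and the early-only rates are assumptions, and stacking the 3-month record is an inference. The sample size of 131 per group reproduces and is unaffected.

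**What to change.** Make the primary analysis a covariate-adjusted logistic model with one record per participant, the 12-month MDE outcome, and delete the random effect over time. Report a 12-month risk contrast with it, for example a standardised risk difference with 95% CI, so that the primary estimate agrees with the planned comparison of proportions. Analyse 3-month MDE in its own model, state its recall window, and use it as an auxiliary variable in the multiple imputation.

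If repeated records are to be kept, the text should name the records, use non-overlapping recall windows, include an arm-by-time term, identify the 12-month contrast as primary, and report marginal (GEE or standardised) estimates.

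The cost is wording in the protocol and analysis plan. No extra participants or data are needed, and the recommended analysis is simpler than the planned one.

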### Exclusion criteria

Individuals who (1) cannot provide informed consent, (2) do not agree to be followed, (3) cannot communicate in English and French, and (4) report suicide behaviors (score > 0 on item 9 of the Patient Health Questionnaire (31) PHQ-9). Individuals with suicide behaviours should be directed for medical attention.

*The intervention* has two integrated components: PDRC and coach-guidance. The PDRC has five sections: (1) individualized depression risk, the interpretation of the risk information, and the national average risk. (2) Factors contributing to the risk. These are the modifiable risk factors the person is currently exposed to, based on the MVRPs and participant self-report. (3) A graphical presentation of their risk and national average risk, and (4) Evidence-based self-help strategies the person currently engages in, and the self-help strategies [32] the person is encouraged to use. The PDRC will be sent to participants by email/mail within two days after the baseline and follow-up assessments.

The coach will contact the participant within a week after the PDRC is provided by telephone or video conference, depending on participants’ preference. The role of the coach is to assist the participant in understanding and interpreting the PDRC, answering their questions, and helping identify self-help strategies that are feasible for the participant; they do not provide psychotherapy. The coaching session will follow the four processes of MI [28]: (1) engaging participants in a mutually trusting and respectful working relationship, (2) focusing on the goals for risk communication, (3) evoking and strengthening motivation for taking self-help strategies, and (4) planning and implementing self-help strategies. A coaching manual has been developed to ensure coaching fidelity, and the fidelity level in our pilot RCT was 97%. The coaching sessions will be audio recorded and reviewed at weekly team meeting to ensure coaching fidelity, with 20% of the sessions be rated by two independent raters for reliability. The coaching manual covers the elements that are essential to include (e.g., asking for commitment) and not include (e.g., providing unsolicited advice) during the coaching sessions. The same procedures will be used for follow-up coaching sessions at 3 months. Communications beyond the scheduled coaching will not be allowed to ensure that participants receive same type of intervention.

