### The control group

Participants in the control group will receive their individualized depression risk information. Receiving individualized depression risk information is considered as “control” because: (1) our previous RCT showed that receiving individualized depression risk information caused no psychological harm and was effective in reducing distress and improving function [33]; (2) receiving depression risk information was used as control in our pilot study; (3) the pilot study suggested that the coach-guided PDRC may be more effective than receiving depression risk information alone.

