### Blinding

The survey firm will securely transfer encrypted baseline data to the project coordinator on a daily basis, with the group assignment data in a separate file. The follow-up assessments will be conducted at the principal investigator’s (PI) telephone interview laboratory at Dalhousie University. Over the study period, investigators will be blinded to participants’ group status. The survey firm interviewers who conduct baseline assessment and randomization, will not be involved in follow-up interviews. The interviewers who conduct the follow-up interviews will not have access to participants’ group status. The coaches will not be involved in follow-up assessments. Given our description of study objectives, participants may know their group status. After the 12-month interview, group status will be linked with interview data by study ID numbers. At the follow-up assessments, if participants develop an MDE, they will be encouraged to contact their family doctor and information about local mental health resources will be provided.

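### Several coaches treat the intervention arm only, but the primary model as described handles only within-participant correlation; if outcomes vary by coach, type I error may exceed 5%

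*Protocol article*

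**What the plan says.** The intervention paragraphs (Protocol article, under Exclusion criteria) describe individual contact: "The coach will contact the participant within a week after the PDRC is provided by telephone or video conference". A second round follows: "The same procedures will be used for follow-up coaching sessions at 3 months". The control arm has no coach: "Participants in the control group will receive their individualized depression risk information" (The control group). That there is more than one coach follows from the plural in Blinding: "The coaches will not be involved in follow-up assessments". The number of coaches, their caseloads and the way participants are assigned to them are not given.

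The primary outcome is the proportion with MDE at 12 months, "measured by the 12-month version of CIDI-MD". Under Statistical analysis, "mixed-effects logistic regression modeling will be performed using combined imputed datasets based on Rubin’s rules", with covariate adjustment, and "it will account for within-participant correlation over time through the incorporation of random effects". That is the only role given to the random effects. Main secondary outcomes are compared with t and chi-square tests. The sample size section contains no design effect.

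**The concern.** This is a partially nested design. With 1,000 participants randomised 1:1, about 500 people share the coaches, and each control stands alone. The sessions follow motivational interviewing and rest on the relationship between coach and participant, so some coaches may do better than others. If so, outcomes under the same coach are correlated, in one arm only.

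A participant-level random effect deals with the 3- and 12-month measurements on one person. It does not deal with correlation between different people who share a coach. The model would then count coached participants as more independent than they are, and the confidence interval for the effect on MDE would be too narrow. The Discussion aims at community implementation, so inference should extend beyond the particular coaches employed in this trial.

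**Working it through.** **The plan's own figure.** Inputs from Sample size calculation: 1.7% versus 9.7%, α = 0.05, and 0.80 (printed as β, read here as power). Two-sided, pooled variance under the null, with mean risk 0.057:

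n = [1.96 × √(2 × 0.057 × 0.943) + 0.8416 × √(0.017 × 0.983 + 0.097 × 0.903)]² / 0.08² = (0.6426 + 0.2718)² / 0.0064 ≈ 130.7, so 131 per arm and 262 in total.

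The stated 262 is reproduced exactly with independent observations and no design effect.

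**Number analysed.** 500 per sex at 1:1 gives 250 per arm; at the assumed 80% response, 250 × 0.80 = 200 per arm within a sex. The article analyses the sexes separately first, so this is the main case.

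**Effect of ignoring coach.** The number of coaches k and the ICC are assumptions; the article gives neither.

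- Caseload: m = 200 / k.
- Design effect, coached arm only: DE = 1 + (m − 1) × ICC.
- Ratio of true to assumed variance of the difference, with equal arms and no average effect: (DE + 1) / 2.
- Actual two-sided type I error: 2 × [1 − Φ(1.96 / √((DE + 1) / 2))].

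Example with k = 5 and ICC = 0.01: m = 40; DE = 1 + 39 × 0.01 = 1.39; variance ratio 1.195; 1.96 / √1.195 = 1.793; type I error 7.3%.

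| Coaches (assumed) | ICC 0 | ICC 0.01 | ICC 0.02 | ICC 0.05 |
|---|---|---|---|---|
| 5 | 5.0% | 7.3% | 9.6% | 16.3% |
| 10 | 5.0% | 6.1% | 7.2% | 10.7% |
| 20 | 5.0% | 5.5% | 6.0% | 7.7% |

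**Simulation check.** Coach-specific risks were drawn from a beta distribution with mean 9.7%, with 200,000 runs per cell and a z-test that ignores coach. At ICC 0 / 0.01 / 0.05, type I error was 4.7% / 7.1% / 16.1% with 5 coaches and 4.8% / 5.9% / 10.4% with 10. These agree with the formula.

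**Sexes combined.** With 400 per arm and the same coaches seeing both sexes, 5 coaches give 9.7% (ICC 0.01) and 25.6% (ICC 0.05); 10 coaches give 7.3% and 16.3%.

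**What these ICCs mean.** The between-coach standard deviation in risk is √(ICC × 0.097 × 0.903). At ICC 0.01 it is 3.0 percentage points; at ICC 0.05 it is 6.6 points, so that coaches one standard deviation either side of the mean would have MDE risks of about 3% and 16%.

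**Can a coach term be estimated?** At the planned 1.7%, 200 coached women yield 200 × 0.017 = 3.4 expected events.

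**The case against.** The strongest reply is that inflation needs a coach ICC above 0, and the article does not show one. If coaching changes nobody's outcome and caseloads do not differ in prognosis, there is no coach variance and the test keeps its 5%. Inflation arises when coach effects differ around a zero average, or when caseloads differ in prognosis. This stands, and the point is therefore conditional.

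The design also limits coach variation: a manual, 97% fidelity in the pilot, weekly review of recordings, double rating of 20% of sessions, no contact outside scheduled sessions, and outcomes taken by interviewers without access to group status. This makes the ICC 0.05 column unlikely. It does not make the ICC zero: fidelity measures adherence to the manual, not equality of results, and with 40 analysed participants per coach even ICC 0.01 has an effect.

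Third, a coach random effect on top of a participant random effect may not be estimable with 3 to 4 events in the coached arm. This also stands, and is why the fix does not insist on changing the primary model.

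Last, the text does not exclude a coach term, and an analysis plan that is not shown may contain one. That is possible. But the article does state what the random effects are for, and that stated purpose does not cover coaches.

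**Conclusion.** The point holds in conditional form. The partially nested structure is documented, and the model as described does not account for it. If the coach ICC is above 0, the standard errors are too small and type I error may exceed 5%: about 5.5% to 7.3% at ICC 0.01 and 7.7% to 16.3% at ICC 0.05, for 20 down to 5 coaches. These figures rest on assumed coach numbers and ICCs, equal caseloads, 200 analysed per arm within one sex, and an unadjusted 12-month comparison of proportions rather than the full adjusted model.

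A reader might infer that false positives certainly exceed 5%, or that the error rate is in the region of 20%. The documents support neither. At ICC 0 the rate is 5.0% whatever the number of coaches, and the high figures need both few coaches and a large ICC.

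**What to change.** State how many coaches there are and how participants are assigned to them. Record coach ID for each intervention participant; the article does not say that it is kept in the data set. Pre-specify a partially nested analysis: clustering by coach in the intervention arm only, each control as their own cluster, with a small-sample-corrected variance. Make it a sensitivity analysis alongside the primary model, or the primary model if the numbers of coaches and events allow it to be estimated. Report the coach ICC.

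The cost is a short addition to the analysis section and one variable, best captured prospectively. Intervals will be somewhat wider, and the coach variance will be imprecise with few coaches or events. Power should hold up: with 5 coaches, 200 women per arm and the planned risks, |0.017 − 0.097| / √[(0.017 × 0.983 × DE + 0.097 × 0.903) / 200] − 1.96 gives 93.9% at ICC 0, 92.5% at ICC 0.01 and 86.4% at ICC 0.05, before any further loss from the small-sample correction.
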